#### Analysis methods

The spot and the 24-hour urine samples from each individual will be analysed separately for sodium, potassium and creatinine. All analyses will be done by local laboratories in Samoa and Fiji using the ion selective electrode method for sodium and potassium analysis and the buffered kinetic Jaffe reaction without de-proteinisation for urine creatinine assay. Age and sex specific estimates obtained from the survey will be weighted based on population data from the most recent census. Descriptive statistics will be reported for anthropometrics, consumer awareness and urinary sodium levels. Results will be reported by sex age groups and evidence for differences between subgroups examined using t-tests.

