### Outcomes

#### Primary

The primary outcome of the study will be the change in 24-hour urinary salt level in the overall study population (in each country). If a positive impact is demonstrated, then a cost-effectiveness assessment will also be undertaken.

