#### Sampling strategy

The study population will be adults aged 18–69 years in both countries. Baseline salt assessment and questions on knowledge, attitudes and behaviours related to salt (KAB) will be integrated into the WHO STEPS survey in Samoa and the STEPS sampling framework will be used in Fiji. The framework uses a stratified (province or division) three-stage (enumeration area, household and individual) cluster random sampling process using probability proportional to size to obtain representative samples for the STEPS survey in each country based on the statistical regions identified in recent Censuses [36-38]. Sub-samples (e.g. every fifth person, so as to recruit 250 men and 250 women) will then be selected to collect 24-hour and spot urines.

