#### Sample size

The sample size for each survey has been calculated to provide precise estimates of the average level of salt separately in adult Samoans and Fijians, based on the 24-hour urine collections. Five hundred participants recruited in both Fiji and Samoa will allow reporting of the mean level of sodium intake to within +/− 4.2 mmol with 95% confidence for each country. This estimate assumes a mean intake of 160 mmol sodium per day with a standard deviation of 48 mmol (1 gram of salt = 17.1 mmol sodium). This sample size will also enable the mean level of sodium to be reported to within +/− 5.85 mmol, for men and women and for rural and urban areas (where the sample is effectively divided in two with a sample size of 250 in each group), and to within +/− 8.42 mmol for subgroups such as older vs. younger men or rural versus urban women (where there will be a sample size of about 125 for each group). There will also be 80% power (alpha = 0.05) to detect approximately 8.5 mmol (0.5 gram salt) or greater differences between the average sodium levels between baseline and follow-up for each country.

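### Subgroup differences are to be examined with unqualified t-tests, which do not fit a stratified, clustered, census-weighted survey

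*Protocol article*

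**What the plan says.** Under Sampling strategy for the population surveys, the design is explicit: "The framework uses a stratified (province or division) three-stage (enumeration area, household and individual) cluster random sampling process using probability proportional to size". The urine sample is then taken from within it: "Sub-samples (e.g. every fifth person, so as to recruit 250 men and 250 women) will then be selected" for 24-hour and spot collections.

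Under Analysis methods for the same surveys, "Age and sex specific estimates obtained from the survey will be weighted based on population data from the most recent census". Two sentences later, after saying that results will be given by sex and age group, the article plans to have "evidence for differences between subgroups examined using t-tests". This is the only inferential method named for the urine and questionnaire data. Nowhere does the article mention design-based or cluster-robust variance, strata in the analysis, or a design effect.

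Under Sample size, men and women, and rural and urban areas, are named as groups for which means will be reported, at 250 people each. The same section gives the planning assumptions: "This estimate assumes a mean intake of 160 mmol sodium per day with a standard deviation of 48 mmol".

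**The concern.** A standard two-sample t-test takes every observation as independent and gives each the same weight. By the article's own description these data are neither. People in one enumeration area share food supply, income and habits, so their sodium values are likely to be correlated, and the census weights make some people count more than others.

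Two things follow. First, the p-value belongs to a different comparison from the one reported: it tests unweighted means while weighted means are printed next to it, and the two can disagree. Second, the standard error is wrong by an amount that depends on the contrast. Where whole enumeration areas fall on one side or the other (rural versus urban), positive correlation makes the naive standard error too small. Where both groups occur within each area (men versus women), the shared area effect largely cancels and the naive standard error is about right or a little too large, before any effect of unequal weights.

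**Working it through.** **Inputs from the article (Sample size):** SD 48 mmol; 500 people per country per survey; 250 and about 125 in subgroups; 80% power at alpha 0.05 for 8.5 mmol. **Not given:** intracluster correlation (ICC), people per enumeration area, design effect (deff), variation of the weights. These are assumed below and shown as ranges.

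**Step 1: do the article's own figures allow for the design?** Half-width under simple random sampling = 1.96 × 48 / √n.

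- n = 500: 1.96 × 48 / √500 = 4.21 (stated 4.2); implied deff (4.2 / 4.207)² = 1.00.
- n = 250: 1.96 × 48 / √250 = 5.95 (stated 5.85); implied deff 0.97. The gap is small and may be a digit slip.
- n = 125: 1.96 × 48 / √125 = 8.41 (stated 8.42); implied deff 1.00.
- Detectable difference between surveys: (1.96 + 0.84) × 48 × √(2/500) = 8.5 mmol, as stated.

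The planning figures therefore treat the 500 as independent people. That agrees with the plain reading of the t-test sentence.

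**Step 2: true size of a nominal 5% t-test when the real variance is deff times the naive one.** Size = 2 × [1 − Φ(1.96 / √deff)].

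- deff 1.08: 1.96 / 1.039 = 1.886, size 5.9%
- deff 1.2: 1.96 / 1.095 = 1.789, size 7.4%
- deff 1.5: 1.96 / 1.225 = 1.600, size 11.0%
- deff 2.0: 1.96 / 1.414 = 1.386, size 16.6%

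**Step 3: what gives such design effects for a between-area contrast.** With m people per area, deff = 1 + (m − 1) × ICC. Cells show deff and the resulting size.

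| m (assumed) | ICC 0.01 | ICC 0.02 | ICC 0.05 |
|---|---|---|---|
| 5 | 1.04, 5.5% | 1.08, 5.9% | 1.20, 7.4% |
| 10 | 1.09, 6.0% | 1.18, 7.1% | 1.45, 10.4% |
| 20 | 1.19, 7.2% | 1.38, 9.5% | 1.95, 16.0% |

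The urine sub-sample takes only some of the people surveyed in each area (every fifth is the example given), which favours the upper rows. Stratification by province or division could lower every entry. Unequal weights would raise them, by an amount that the article does not allow one to compute.

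**Step 4: a within-area contrast.** If each area contributes equal numbers of men and women, the area effect cancels and the true variance is about (1 − ICC) times the naive one. At ICC 0.05, size = 2 × [1 − Φ(1.96 / √0.95)] = 2 × [1 − Φ(2.011)] = 4.4%. At ICC 0.02, it is 2 × [1 − Φ(1.980)] = 4.8%. The error here is small and on the conservative side.

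**The case against.** The strongest reply is that a condensed article need not describe variance estimation. Survey software reports t statistics for weighted means, and the text does not say that the tests are unweighted or ignore the clusters. A design-based t-test is therefore conceivable. What stands is that the authors may intend one. But the article names a method rather than leaving it open, names it without qualification, and its planning figures carry a design effect of 1.00.

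A second reply is that the groups named beside the t-tests are sex and age groups, which lie mostly within enumeration areas, where little harm is expected. That also stands. The anti-conservative case concerns rural versus urban, which appears as a reporting group under Sample size and not in the t-test sentence itself.

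Two stronger readings go beyond the text. A reader might infer that the primary result, the change in 24-hour urinary salt between surveys, will be tested with an ordinary t-test at an inflated false-positive rate. The t-test sentence covers subgroup differences only, and no test is named for the change. The power statement uses the independent-samples formula, but a planning formula is not an analysis method. Nor does the article say whether follow-up uses different enumeration areas; shared areas would reduce the variance of the change. A reader might also infer that shifts in age or sex mix between surveys go uncorrected. Census weighting of age- and sex-specific estimates already addresses those in the reported means.

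**Conclusion.** The point holds for the subgroup tests. A method is stated that does not fit the stated sampling and weighting, and nothing elsewhere in the article corrects it.

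The size of the error cannot be fixed from the article. Under the assumed design effects of 1.08 to 2.0, a between-area contrast tested at a nominal 5% has a true size of about 6% to 17%. With 5 to 10 people per area and an ICC of 0.02 to 0.05, the range is about 6% to 10%. These figures assume equal-sized areas and no gain from stratification, and leave out unequal weights. For men versus women, clustering alone leaves the test near or slightly below 5%. The mismatch between unweighted p-values and weighted estimates applies to every contrast. For the primary change, the article shows only a power calculation with no design allowance, not a wrong test.

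**What to change.** In Analysis methods for the population surveys, replace the t-tests with survey-weighted comparisons: survey linear regression or adjusted Wald tests that declare province or division as strata, the enumeration area as primary sampling unit, and the sampling and census weights, with Taylor-linearised variance. Add one sentence stating that the 2012–2015 change in each country will be estimated with the same design-based variance. The subgroup comparisons stay as differences in level between groups, as the article plans them.

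The cost is a change of wording and a standard survey procedure. Stratum and enumeration-area identifiers must be kept in the analysis files of both surveys. Intervals will usually be somewhat wider for between-area contrasts and for the change.

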### Surveys of the salt content of foods for sale in shops

#### Sampling strategy

The salt levels in the foods that contribute most to salt in the diet (identified through the FFQs) will be monitored according to published protocols [41] with the largest stores in the main urban centres of Fiji (Suva) and Samoa (Apia) included in the surveys. Additional chemical analysis of the sodium content of the main meals eaten in and out of the home will be undertaken by national government laboratories in each country.

#### Data collection and management

The food composition data will be collected primarily from printed information on the front and back of the product labels, including the nutrition information panel. The minimum data fields collected for each product will be country of origin, brand/manufacturer, product name, food category, serving size and sodium content per 100 g and/or per serving. Direct chemical analysis of the sodium content of a sub-sample of products will be undertaken to assess the accuracy of the sodium content listed on the nutrition labels. Direct chemical analysis will also be used to obtain sodium content data for products and meals that have been identified through the FFQ as contributing significantly to salt in the diet and that are unpackaged or do not display a nutrient declaration.

#### Analysis methods

The primary analysis will compare the mean concentration of sodium in foods before and after the salt reduction intervention has been implemented. Subsidiary analyses will explore changes in sodium levels in different food types and for the foods marketed by different manufacturers.

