### Study objectives

The overall study objective is to assess the effect of a multi-pronged, cross-sectoral intervention program to reduce population salt intake in both Fiji and Samoa. Secondary objectives include determining the effects of the salt reduction program on population knowledge, attitudes and behaviour by comparing mean population levels at baseline and follow-up and determining the effects of the salt reduction program on average levels of sodium in foods based upon food composition surveys that collect data from food labels at baseline and follow-up. The project will also consider the effects of the salt reduction intervention on dietary salt by examining changes in diet based on the Food Frequency Questionnaires (FFQs) administered at baseline and follow-up in each country. The relationship between salt intake measured by 24-hour urine and salt intake estimated from spot urine will also be explored.

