#### Secondary outcomes

The main secondary outcomes will be changes in knowledge levels and current practices relating to salt and changes in the mean concentration of sodium in foods.

Additional outcomes will include changes in the composition of diet based on the FFQs and understanding of the relationship between salt intake measured by spot and 24-hour urine in each country. The latter is important as, if it proves possible to use spot urines to estimate 24-hour urinary sodium excretion, in future this would provide a more feasible and practical alternative to measuring salt intake for countries.

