#### Salt reduction intervention

While the nature of the salt reduction intervention strategies will be informed by the outcome of the stakeholder consultation and other baseline data collected during the project, it is likely that the program will include core components and approaches employed elsewhere. In addition, the strategies will reinforce existing national programs being implemented by the Ministry of Health and key agencies in each country. Core components of the programs will include: (i) the food industry (including caterers, bakers, importers, processors and retailers) with efforts directed towards reducing average salt levels in locally manufactured and imported foods towards agreed targets for salt levels in foods, work to facilitate the catering and food service sectors to provide low salt meals and initiatives related to labelling of foods in stores and food service outlets; (ii) consumers through targeted and sustained campaigns to change awareness and behaviours related to salt with a focus on children and using culturally appropriate communication channels including church leaders and women’s groups; and (iii) settings such as schools, hospitals and the workplace through the establishment of standards and educational campaigns.

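### The main food-sodium comparison rests on one overall mean with no stated category weights, so a change in product mix between rounds may create, mask or reverse an apparent change

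*Protocol article*

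**What the plan says.** Under the shop surveys, Analysis methods, the protocol article states: "The primary analysis will compare the mean concentration of sodium in foods before and after the salt reduction intervention has been implemented". The next sentence sets the rank of the category results: "Subsidiary analyses will explore changes in sodium levels in different food types and for the foods marketed by different manufacturers". No weights, standardisation or product matching are mentioned.

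The analysis serves one of the main secondary outcomes, listed under Secondary outcomes as "changes in the mean concentration of sodium in foods".

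Two other parts of the shop-survey section matter here. Sampling strategy limits which foods are surveyed: "The salt levels in the foods that contribute most to salt in the diet (identified through the FFQs) will be monitored according to published protocols". Data collection and management says "The food composition data will be collected primarily from printed information on the front and back of the product labels". It also plans chemical analysis for products that the food frequency questionnaire (FFQ) shows to be important and that carry no nutrient declaration. The minimum fields for each product include brand or manufacturer, product name and food category. Sales volume is not among them.

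**The concern.** The Background names bread, margarine, crackers, noodles, canned foods, butter, and soy and other sauces as the high-sodium staples. Sodium per 100 g is very unlike across such a list. A single mean over all listed products therefore mixes two things: the sodium content of foods within each category, and the share of listed products in each category. If stores carry more sauces and fewer breads at follow-up, the mean rises although no recipe has changed.

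This comparison is the study's direct evidence on the food-industry component of the programme. If the overall mean and the category results disagree, the plan as written gives precedence to the overall mean, which is the one exposed to mix. Settling that after the follow-up data are seen would be a post hoc choice.

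**Working it through.** The article gives no product counts, category means, standard deviation or target change for the food survey, so there is no figure of its own to reproduce. All sodium values and shares below are assumptions, chosen to show the mechanism and its range.

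**Decomposition.** Let w be a category's share of listed products and m its mean sodium, with 0 for baseline and 1 for follow-up. The overall mean is Σ w·m, and its change splits exactly into

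Σ w0·(m1 − m0) + Σ (w1 − w0)·m1.

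The first term is the within-category change at the baseline mix. The second is the mix shift. The overall comparison reports the sum; a comparison with fixed baseline weights reports the first term alone.

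**Illustration A: two groups, 2,000 and 400 mg/100 g.**
- Baseline, 10% high-sodium: 0.10×2000 + 0.90×400 = 560.
- Follow-up, 15% high-sodium, no product changed: 0.15×2000 + 0.85×400 = 640. Ratio 640/560 = 1.143, or +14%.
- Follow-up, 5% high-sodium, no product changed: 0.05×2000 + 0.95×400 = 480. Ratio 480/560 = 0.857, or −14%.
- Follow-up, 15% high-sodium and every product cut by 10%: 0.9×640 = 576. Ratio 576/560 = 1.029, or +2.9%, although every product fell by 10%.

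**Illustration B: four groups.** Assumed means: bread 450, noodles 1,000, canned foods 600, sauces 5,000 mg/100 g. Assumed baseline shares: 30%, 25%, 35%, 10%. Baseline mean: 0.30×450 + 0.25×1000 + 0.35×600 + 0.10×5000 = 135 + 250 + 210 + 500 = 1,095 mg/100 g. The sauce share is then varied and the other three are rescaled in proportion. Their joint mean is 595/0.90 = 661.1, so the follow-up mean with no reformulation is (1 − s)×661.1 + s×5000 for sauce share s.

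| Sauce share at follow-up | Overall mean, no product changed | Overall mean, every product cut 10% |
|---|---|---|
| 5% | −19.8% | −27.8% |
| 8% | −7.9% | −17.1% |
| 10% | 0.0% | −10.0% |
| 12% | +7.9% | −2.9% |
| 15% | +19.8% | +7.8% |

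For example, at 15%: 0.85×661.1 + 0.15×5000 = 1,311.9, and 1,311.9/1,095 = 1.198. With the 10% cut: 0.9×1,311.9 = 1,180.7, and 1,180.7/1,095 = 1.078.

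Standardised to the baseline mix, the result is 0% in every row of the second column and −10% in every row of the third.

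**The case against.** **The declared outcome is average sodium in foods, not reformulation.** Importers and retailers are among the programme's targets, and they could lower the average by changing what they stock. On that view a mix shift is part of the effect. This has force, and it is a reason to keep the overall mean in the report. It does not rescue it as the main contrast: with no sales or intake weights stated, a mean over listed products is neither a market average nor an intake average. One more slow-selling sauce counts as much as one more staple bread.

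**Weighting may be in the full plan or in the cited survey protocol.** Neither is shown, and the article never says the mean is unweighted. That is fair. But the article does fix the order of the analyses, with the overall mean as main and food type as exploratory, and that order is the point at issue.

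**Several stronger readings are tempting but not supported.**
- A reader might infer that the survey takes whatever products happen to be found. Sampling strategy instead selects foods by their contribution to dietary salt and follows a published protocol. That limits the food types, but not the number of products per type at each round.
- The programme includes "initiatives related to labelling of foods in stores and food service outlets", so a reader might infer that products without labels are lost and that growing label coverage biases the result. The planned chemical analysis of FFQ-important products without a nutrient declaration largely answers this.
- A reader might infer that the food list is redrawn from the follow-up FFQ. The article says the FFQ is repeated to examine diet; it does not say the list is redrawn.

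**Conclusion.** The point holds in limited form. The article makes a before/after comparison of one overall mean the main analysis of a main secondary outcome, makes food-type changes subsidiary, and states no fixed category weights. A change between rounds in the number of products per category may then create, mask or reverse an apparent change.

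On the assumed values, a move of five percentage points in a high-sodium group shifts the mean by about 14% (two groups) or 20% (four groups) in either direction with no product changed. In the upward direction it turns a uniform 10% cut into an apparent rise. These sizes depend wholly on the assumed category means and shares. If the mix stays the same, the overall mean is not distorted. The documents do not say how the mix will move, so bias is possible rather than predicted.

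The primary outcome, 24-hour urinary salt, does not depend on this analysis.

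**What to change.** Before follow-up food data are examined:

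1. Make the main contrast the change in mean sodium within food category, averaged over a category list fixed at baseline with fixed baseline weights. Each category's contribution to salt intake in the baseline FFQ is a natural choice of weight.
2. Report the overall unweighted mean as descriptive, so that shifts in the product range remain visible.
3. Add a sensitivity analysis of products found in both rounds, matched on brand and product name. Category standardisation does not deal with products entering and leaving within a category; this shows how much they matter.

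The cost is wording and modest analysis time, since food category, brand and product name are already minimum data fields. The downside is that between-category shifts in what is stocked no longer count in the main estimate, and new products enter it only through their category mean. The descriptive overall mean covers the first of these.

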### Development of the salt reduction program

The development of the salt reduction program will be under-pinned by participatory community research [42] to obtain a comprehensive understanding of consumer and stakeholder opinions in relation to the most effective mechanisms for reducing salt intake. Stakeholder consultation will be conducted in both Fiji and Samoa and, while it is anticipated to be considerable overlap in the findings, the different structural social and cultural factors in each country will be carefully considered.

